| Study Design                | Multicenter, prospective, randomized, double-blinded, placebo-controlled study                                                                                                                                                                                                                                                                                                                                                                                                                                                                                                                                       |
| Purposes                    | The primary study objective is to determine the risks of 12 months of DAPT vs 6 months of DAPT followed by 6 months of aspirin monotherapy or clopidogrel monotherapy on gastrointestinal mucosal injury after DES implantation.
The secondary objective is to evaluate the feasibility and safety of AMCE as a method for detecting gastrointestinal mucosal injury and bleeding in patients receiving APT.
The exploratory objective is to establish a gastrointestinal mucosal injury scoring system that may identify patients at future risk for clinical gastrointestinal bleeding during long-term APT. |
| Randomization               | All enrolled patients after PCI firstly received DAPT as a composite of aspirin plus clopidogrel for 6 months, and are then randomly assigned in a 1:1:1 ratio to receive:
A: aspirin plus clopidogrel, for an additional 6 months;
B: aspirin plus clopidogrel-placebo, for an additional 6 months;
C: aspirin-placebo plus clopidogrel plus for an additional 6 months.                                                                                                                                                                                                                                   |

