## 12.2 Methods of statistical analyses

Continuous variables will be summarised as the number of observations, number of missing values, mean, standard deviation, median, quartiles, and range.

Categorical variables will be summarised as the number of observations, number of missing values, frequencies, and percentages.

Baseline clinical, demographic, laboratory and procedural characteristics will be summarized by randomized treatment group.

Demographic and baseline characteristics will be summarized by randomized treatment group and for all randomized subjects combined (i.e., FAS population). Baseline characteristics that will define subgroups of interest for the efficacy and safety analyses are:

- Age group ( $< 65$ ,  $\geq 65$  years)
- Gender (Male, Female)
- Diabetes mellitus (yes, no)
- Chronic kidney disease (yes, no)
- CAD presentation (Stable, Unstable)
- HP infection status at enrollment (positive, negative)
- Antiplatelet treatment status at enrollment ( $>6$  months,  $\leq 6$  month)

**Censoring:** Subjects not experiencing any endpoint will be censored at time of death, last contact date (for subjects who withdraw consent or are lost to follow-up) or 180-day  $\pm$  14 days after randomization, whichever comes first.

**Primary Efficacy Analysis:** The primary endpoint analysis will be conducted according to the intention-to-treat (ITT) principle. The main aim of this study is to determine whether the strategy of 6-month DAPT plus 6-month single antiplatelet therapy is superior to 12-month DAPT in terms of the primary endpoint (gastrointestinal injury) after contemporary DES implantation. The null hypothesis ( $H_0$ ) for this analysis is that the incidence of primary endpoint in the experimental group is same as that of the control group, namely  $P_0=P_1$ . The alternative hypothesis ( $H_1$ ) is that the incidences of primary endpoints in the two groups was not equal, namely  $P_0 \neq P_1$ , and the superiority test is conducted at the 2-sided significance level of 0.05. This analysis will be repeated in the Per-protocol (PP) population to support the main results.

The primary and secondary endpoints will be also analyzed in the following clinically

relevant pre-specified subgroups (Part 12.2). Formal interaction testing will be performed using the subgroup  $\times$  treatment allocation as an additional term in the logistic models.

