## **3 Study Design**

### **3.1 Overall study design and flow chart**

The OPT-PEACE is a multicenter, randomized, double-blind, placebo-controlled trial to evaluate the efficacy and safety of antiplatelet monotherapy with aspirin or clopidogrel between 6 and 12 months after DES implantation following 6 months of

DAPT detected by AMCE. All enrolled patients with a negative screening AMCE examination will be treated with open-label aspirin (100 mg/d) plus clopidogrel (75 mg/d) for 6 months. After 6 months, patients free from interval major adverse ischemic or clinically overt bleeding events and otherwise without any exclusion criteria (**section 3.2**) will undergo a second AMCE examination before randomization. Patients successfully completing this exam are then randomly assigned in a 1:1:1 ratio to receive aspirin plus clopidogrel, aspirin plus clopidogrel-placebo or clopidogrel plus aspirin-placebo for an additional 6 months in a double blinded manner.

[figure not shown]

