## **6 Analysis sets**

### **6.1 Full analysis set (FAS)**

All patients who have been randomized to study treatment will be included irrespective of their protocol adherence and continued participation in the study. Patients will be analysed according to their randomized study drug assignment (not to which treatment they actually received) irrespective of whether the event occurred before or following discontinuation of study drug. Patients who withdraw consent to participate in the study (or are lost to follow-up) will be included up to the date of

their study termination except for vital status known through public records (for use in the analyses of deaths). All primary, secondary, and exploratory efficacy variables will be analyzed using the FAS. The primary endpoint of gastric or intestinal mucosal injury will be analyzed in a modified intention to treat (mITT) population, (i.e., patients with valid primary endpoint results). Unless otherwise stated, the FAS will be considered the primary analysis set for the primary and secondary variables and for the exploratory variables.

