## **6.3 Safety analysis set**

There are 2 safety sets (SSs) in OPT-PEACE trial. Safety and tolerability will be assessed from serious adverse events (SAEs) and adverse events (AEs). The assessment will include MACCE defined as a composite of cardiac death, target lesion MI, ischemic stroke, clinical-driven TLR or stroke in SS (investigational drug) and the incidence of AEs related to AMCE examination and capsule retention in SS (AMCE examination). All events will be independently adjudicated.

The first safety analysis set includes patients who received at least 1 dose of study drugs (aspirin, clopidogrel, and/or matching placebos) and who have data observed at any time after first randomized dose until the end of the study. The safety endpoint is MACCE defined as a composite of cardiac death, target lesion MI, ischemic stroke, clinical-driven TLR or stroke within 12 months after enrollment. Throughout the safety results sections, erroneously treated patients (patients randomized to one of the treatment groups but actually given the other treatment) will be accounted for in the actual treatment group. Patients with erroneous treatment would be analyzed according to that treatment only if they only received the erroneous treatment and none of the correct treatment.

The secondary safety analysis set includes patients who received AMCE exam at least once and observed up to 30 days for safety surveillance. The safety analysis set will be considered the primary analysis set for AMCE as a method for detecting gastrointestinal mucosal injury and bleeding. The safety endpoint is 1) adverse events, defined as symptoms or signs such as abdominal distension, nausea, or vomiting; 2) capsule retention (i.e., a capsule endoscope remaining in the digestive tract for a minimum of 2 weeks or a capsule endoscope that requires directed intervention or therapy to aid its passage).

All safety variables will be analyzed using the safety analysis set.

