### 9.3.1 Analysis for categorical and ordinal endpoints

#### **Binary variables include:**

- The incidence and severity of gastric and intestinal mucosal lesions during the first 6 months after study enrollment (prior to randomization);
- The incidence and severity of gastric and intestinal mucosal lesions after randomization (ie, between 6 months and 12 months after study enrollment);
- The incidence of clinically evident gastrointestinal hemorrhage attributed to the upper GI tract (or of unknown origin) during 6 months after study enrollment (prior to randomization);
- The incidence of clinically evident gastrointestinal hemorrhage attributed to the upper GI tract (or of unknown origin) after randomization (ie, between 6 months and 12 months after study enrollment);
- The incidence of clinically evident gastrointestinal hemorrhage attributed to the upper GI tract (or of unknown origin) during 12 months after study enrolment.

Binary variables will be analyzed using logistic regression with treatment as fixed effect factors. Logistic regression model results will be reported as odds ratios for monotherapy group vs. DAPT group, with 95% CIs and p-values.

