### 9.3.2 Analysis for time-to-event endpoints

Kaplan-Meier curves will be plotted by treatment group. Patients not experiencing a endpoint event during corresponding time interval will be censored at the time of death, last contact date (for subjects withdrawing consent or lost to follow-up) or 365 days, whichever comes first.

A hazard ratio (HR) and two-sided 95% CI for the primary endpoint will be generated using the Cox proportional hazards model. The null hypothesis ( $H_0$ ) for this analysis is that the  $HR = 1$ . The two-sided alternative hypothesis ( $H_A$ ) is that the  $HR \neq 1$ . A test of superiority at the two-sided 0.05 level will be performed using a p-value from a log-rank test.

- All bleeding (BARC types 1–5) during the 12 months after enrollment;
- The incidence of target lesion failure (TLF); cardiac death, target-vessel MI, or clinically-driven target lesion revascularization), during the 12 months after enrollment;
- The incidence of net adverse clinical events (NACE, defined as TLF or BARC type 2–5 bleeding) during the 12 months after enrollment;
- The incidence of stent thrombosis (ARC definite, probable, or definite/probable) during the 12 months after enrollment.

In addition, all secondary endpoints will also be compared across the 3 groups, and for all single group versus group comparisons (12-month DAPT vs 6-month DAPT plus 6-month aspirin monotherapy; 12-month DAPT vs 6-month DAPT plus 6-month clopidogrel monotherapy; and 6-month DAPT plus 6-month aspirin monotherapy versus 6-month DAPT plus 6-month clopidogrel monotherapy).

All analysis will be repeated in the PPS to support the primary results.

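### Secondary and drug-safety comparisons between arms run from enrolment although randomisation is six months later, and two endpoints given an arm odds ratio end before randomisation

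*Supplement*

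**What the plan says.** **Time of randomisation.** The synopsis of Protocol v1.4 states: "All enrolled patients after PCI firstly received DAPT as a composite of aspirin plus clopidogrel for 6 months, and are then randomly assigned". Until then everyone takes the same open-label DAPT. SAP 3.1 and 3.3 take forward to the 6-month capsule examination "patients free from interval major adverse ischemic or clinically overt bleeding events". SAP 3.3 then randomises only those whose examination shows no ulceration or bleeding.

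**Time-to-event endpoints.** SAP 9.3.2 plots Kaplan-Meier curves by arm and tests a hazard ratio of 1 (Cox model, log-rank p-value) for all bleeding, TLF, NACE and stent thrombosis. Each is listed over the 12 months after enrolment. Event-free patients are censored at death, last contact "or 365 days, whichever comes first". SAP 9.4 applies the same method to the drug-safety endpoint, which SAP 6.3 gives as "MACCE defined as a composite of cardiac death, target lesion MI, ischemic stroke, clinical-driven TLR or stroke within 12 months after enrollment".

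**Binary endpoints.** SAP 9.3.1 lists "The incidence and severity of gastric and intestinal mucosal lesions during the first 6 months after study enrollment (prior to randomization") (endpoint 1) and the matching upper GI haemorrhage endpoint (endpoint 3). It then says of all the listed binary variables: "Logistic regression model results will be reported as odds ratios for monotherapy group vs. DAPT group", with confidence intervals and p-values. SAP 9.3.2 adds three-group and pairwise comparisons for all secondary endpoints. On the population, SAP 6.1 says: "All primary, secondary, and exploratory efficacy variables will be analyzed using the FAS".

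**Text pointing the other way.** Endpoints 2 and 4 are wholly post-randomisation. SAP 4.2 names a window of six months after randomisation for symptoms, bleeding, NACE and stent thrombosis, alongside the 12-month one. Protocol 12.2 censors at 180 days, plus or minus "14 days after randomization, whichever comes first".

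**The concern.** Randomisation makes the arms comparable from the day of assignment, and treatment can act only from that day. Roughly 180 of the 365 days analysed come earlier, when the arms are on identical drugs and the true hazard ratio is 1.

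This does different damage to different endpoints:

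- **Bleeding, NACE, symptoms.** Early events that do not bar randomisation fall equally on all arms. In a first-event analysis they also use up the patient's event. The contrast shrinks towards no difference, and the hazard ratio is not constant over the window.
- **TLF and MACCE.** Patients with early events are largely not randomised, so the first six months are nearly event-free by selection. The Kaplan-Meier estimate labelled 12 months then describes about six months of risk in selected patients.
- **Endpoints 1 and 3.** Assignment cannot affect an outcome that precedes it. The null is true by design, so any significant odds ratio is a false positive.

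Bleeding and NACE are the clinical counterpart of the capsule findings, so a diluted result could hide a real benefit of monotherapy.

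**Working it through.** **1. The plan's own power figure.** SAP 5 gives 384 evaluable patients (256 and 128) for 90% power at 47% versus 30%, two-sided 0.05. The pooled two-proportion formula gives 127 + 254 = 381, and 128 versus 256 gives power 90.3%; 384 / 0.8 = 480. The figure reproduces. It concerns the primary endpoint only. No rate or power is stated for the endpoints discussed here.

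**2. Time zero in SAP 9.3.2.** The section states none. If it were randomisation, a 365-day cap would never bind, since randomised follow-up is about 180 days. The cap fits only a clock started at enrolment, which is also how the listed endpoints are worded.

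**3. Where the post-randomisation windows go.**

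| Endpoint | After-randomisation window in SAP 4.2 or 6.3 | Used in SAP 9.3/9.4 or the randomised-cohort shells (SAP 11) |
|---|---|---|
| Lesions (2), GI haemorrhage (4) | Yes, separate endpoints | Yes, in 9.3.1 |
| Symptoms, bleeding, NACE, stent thrombosis | Yes | No |
| TLF, MACCE | None | No |

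**4. Dilution for bleeding (all rates assumed).** Take 160 DAPT and 320 monotherapy patients, with 8% and 4% bleeding after randomisation.

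- Events: 160 × 0.08 + 320 × 0.04 = 25.6.
- True HR = ln(0.96) / ln(0.92) = 0.49; ln HR = −0.714.
- Power = Φ(√(D × 1/3 × 2/3) × |ln HR| − 1.96), where D is the number of events. With D = 25.6 this is Φ(2.385 × 0.714 − 1.96) = 40%.

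Now let a share q of every arm bleed before randomisation. There are 480q early events with HR 1 and 25.6 × (1 − q) later first events. The event-weighted ln HR is −0.714 × later / total. For q = 8%: 38.4 + 23.6 = 62 events, ln HR = −0.714 × 23.6 / 62 = −0.27, HR 0.76, power 17%.

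| Bleeding before randomisation | HR from enrolment | Power |
|---|---|---|
| 0% | 0.49 | 40% |
| 1% | 0.55 | 34% |
| 4% | 0.67 | 24% |
| 8% | 0.76 | 17% |
| 12% | 0.82 | 13% |

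The weighting is an approximation, so it was checked with a Cox simulation (true HR 0.5, 10% six-month control risk, 160 versus 320, 300 runs per setting). Median HR from enrolment was 0.49 with no pre-randomisation hazard, 0.68 with half the later control hazard and 0.76 with an equal hazard. From randomisation it stayed near 0.5.

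**5. TLF and MACCE.** The zero-hazard run is the relevant one: when early events are screened out, the HR is unchanged. What remains wrong is the label on the rate.

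**6. Endpoints 1 and 3 in the FAS.** SAP 10 reports new ulceration or bleeding at the 6-month examination in 18% of patients. They are not randomised, so they are not in the FAS. Erosions do not bar randomisation and remain. Endpoint 3 should be near zero in every arm, since Protocol Appendix 4 (18.2) does not randomise patients with earlier GI bleeding.

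**7. Censoring day.** The last visit can fall after day 365 on each reading of the windows:

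- Visit 3 at 12 months from PCI (Table 2): 365 + 14 = day 379.
- Randomisation at 6 months + 7 days (Table 2), then 180 + 14: 180 + 7 + 194 = day 381.
- Randomisation at 6 months + 2 weeks (SAP 3.3), then 180 + 14: 194 + 194 = day 388.

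**The case against.** The strongest defence has four parts.

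**The windows exist.** SAP 4.2 names post-randomisation windows, and the censoring sentence in SAP 9.3.2 refers to the interval that corresponds to each endpoint. This shows intent. But 9.3.2 lists only the 12-month versions, the cap is fixed, the shells carry only 12 months, and TLF and MACCE have no other window.

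**The objective compares strategies.** It sets 12 months of DAPT against six months followed by monotherapy, so a 12-month cumulative figure is a recognisable summary. That stands for description. It does not justify testing arms on time before they existed.

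**The eligibility check limits the damage.** This largely stands. Patients with overt bleeding or ischaemic events are to be left out, so the lower rows of the dilution table may be the relevant ones. A reader might infer that the TLF and MACCE hazard ratios are also pulled to 1. To the extent that the check works, they are not.

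**The shells already separate the first six months.** Shells 1.1.10.2 and 1.1.10.4 put 6-month injury and haemorrhage under the enrolled cohort, and the randomised-cohort binary shells list only 12 months. The arm odds ratio comes from one general sentence after a list. That makes the repair easy, but the sentence still orders the tests.

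**Conclusion.** The point holds and should be fixed before analysis. SAP 9.3.2 and 9.4 use the wrong time origin for arm comparisons, and SAP 9.3.1 prescribes tests on two outcomes that precede assignment.

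The size is known only conditionally. Dilution for bleeding runs from slight (HR 0.55 for a true 0.49) to severe (0.82) over an assumed 1% to 12% of pre-randomisation bleeding. Even from randomisation, power in the example is only 40%.

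Several stronger readings are tempting, and the documents do not support them:

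- **Every secondary endpoint is affected.** Endpoints 2 and 4 are not.
- **Endpoint 1 is zero in the FAS.** Only its ulcer and bleeding parts are removed; erosions count and remain.
- **One arm is favoured.** Early events fall equally across arms in expectation. The result is lost contrast, with no false benefit.
- **Much randomised follow-up is cut.** At most two to three weeks are lost, in patients with late visits; day 388 is the extreme case.
- **The primary conclusion is at risk.** Nothing here touches the primary analysis or its sample size.

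**What to change.** 1. **SAP 9.3.2 and 9.4.** For arm comparisons, set time zero at randomisation and count events after it. Use the windows already in SAP 4.2, and add one for TLF (4.2) and MACCE (6.3). Treat symptoms in 9.3.1 the same way.
2. **Censoring.** Reconcile the 365-day cap with Protocol 12.2. State one end of randomised follow-up that keeps events up to the final visit, since a tolerance of ±14 days is a visit window and not a censoring date.
3. **SAP 9.3.1 and the pairwise paragraph of 9.3.2.** Remove the arm contrasts for endpoints 1 and 3. Report them, with the first-six-month part of the other endpoints, as single-cohort incidences in patients enrolled after a negative screening examination, using shells 1.1.10.2 and 1.1.10.4. Name that denominator, because Protocol 12.1 defines the enrolled population as everyone who signed consent.
4. **12-month figures.** Keep those counted from enrolment as descriptive, and say that randomised patients were selected at six months.
5. **SAP 11.** Add shells for the post-randomisation windows.

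The cost is SAP wording and a changed time origin in the programs. No new data are needed.

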## 9 Statistical methods

### 9.1 General principles

Statistical analyses will be performed using SAS version 9.3. Unless otherwise stated, all hypothesis tests will be performed using two-sided tests at the 5% significance level. Data will be summarised overall and by treatment group. Continuous variables will be summarised as the number of observations, number of missing values, mean, standard deviation, median, quartiles, and range. Categorical variables will be summarised as the number of observations, number of missing values, frequencies, and percentages. Baseline clinical, demographic, laboratory and procedural characteristics will be summarized by randomized treatment group.

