### 9.2 Analysis for the primary endpoint

The primary objective of OPT-PEACE trial is to determine the impact of 6-month DAPT plus 6-month single antiplatelet therapy versus 12-month DAPT in terms of the primary endpoint (gastrointestinal injury) after contemporary DES implantation. This analysis will be carried out in the FAS. The null hypothesis ( $H_0$ ) for this analysis is that the incidence of primary endpoint in the experimental group is same as that of the control group, namely  $P_0=P_1$ . The alternative hypothesis ( $H_1$ ) is that the incidences of primary endpoints in the two groups was not equal, namely  $P_0 \neq P_1$ , and the superiority test is conducted at the 2-sided significance level of 0.05. An odds ratio (OR) and two-sided 95% CI for the primary endpoint will be generated using the logistic regression model with treatment (monotherapy group vs. DAPT group) as fixed effect factors. This analysis will be repeated in the PPS to support the main results.

In addition, for the purpose of exploration, primary endpoint will also be compared across the 3 groups, and for all single group versus group comparisons (12-month DAPT vs 6-month DAPT plus 6-month aspirin monotherapy; 12-month DAPT vs 6-month DAPT plus 6-month clopidogrel monotherapy; and 6-month DAPT plus 6-month aspirin monotherapy versus 6-month DAPT plus 6-month clopidogrel monotherapy).

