#### **Ordinal variables include:**

- Gastrointestinal symptoms (pain, nausea/vomiting, dysphagia, other) during the 12 months after enrolment (Protocol Appendix 3).

Ordinal outcomes will be compared between groups using proportional odds logistic regression models. Logistic regression model results will be reported as odds ratios for monotherapy group vs. DAPT group, with 95% CIs and p-values.

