## **9.6 Subgroup analysis**

The primary and secondary endpoints will be summarised in clinically relevant subgroups of the FAS as a whole and by treatment group. For each subgrouping variable, ORs and two-sided 95% CI will be calculated within each subgroup using a Logistic regression with treatment as fixed effect factors. Formal interaction testing on the ratio scale will be performed using the subgroup  $\times$  treatment allocation as an additional term in the Logistic model.

The following subgrouping variables will be considered:

- Age (<65 years,  $\geq$ 65 years)
- Sex (male, female)
- Diabetes mellitus (yes, no)
- Chronic kidney disease (eGFR<60,  $\geq$ 60 mL/min/1.73m^2)
- Acute coronary syndrome (yes, no)

- Prior history of gastrointestinal bleeding (<24 months, ≥24 month)
- HP infection status (yes, no)
- DAPT duration prior to randomization (>6 months, ≤6 months)

Another subgroup analysis will be performed in patients in whom follow-up was complete vs incomplete or otherwise affected by the COVID-19 pandemic (6-month visit after randomization date: before 2020/1/23, after 2020/1/23).

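### SAP 9.3.2 sets a two-sided 0.05 superiority test over four secondary endpoints and adds three-group and pairwise comparisons of all secondaries, with no hierarchy, adjustment or exploratory label

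*Supplement*

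**What the plan says.** - SAP 9.1, unless otherwise stated: "all hypothesis tests will be performed using two-sided tests at the 5% significance level".
- SAP 9.2 tests the primary endpoint once, pooled monotherapy against DAPT, by logistic regression. It then adds further contrasts with a label: "In addition, for the purpose of exploration, primary endpoint will also be compared across the 3 groups, and for all single group versus group comparisons".
- SAP 9.3.1 covers five binary secondaries: "Logistic regression model results will be reported as odds ratios for monotherapy group vs. DAPT group, with 95% CIs and p-values". It also covers one ordinal secondary: "Ordinal outcomes will be compared between groups using proportional odds logistic regression models".
- SAP 9.3.2 belongs to the section on secondary endpoints, but it reads: "A hazard ratio (HR) and two-sided 95% CI for the primary endpoint will be generated using the Cox proportional hazards model". It gives null and alternative hypotheses and continues: "A test of superiority at the two-sided 0.05 level will be performed using a p-value from a log-rank test". The list directly beneath holds four secondary endpoints: all bleeding, TLF, NACE and stent thrombosis.
- The same section then extends the contrasts: "In addition, all secondary endpoints will also be compared across the 3 groups, and for all single group versus group comparisons". It does not repeat the label used in 9.2. All analyses are repeated in the per-protocol set.
- SAP 9.6 adds formal interaction tests for the primary and secondary endpoints.

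Neither the SAP nor Protocol V1.4 (sections 11.2 and 12.2) gives a testing order, a gate, an alpha split, or a statement that secondary p-values are descriptive.

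**The concern.** Each secondary endpoint receives five comparisons: one pooled, one three-group and three pairwise. All run at the full 5%. The SAP marks such contrasts as exploratory for the primary endpoint, so the missing mark for the secondaries can be read as deliberate. Nothing in the text would then stop a single p<0.05 (less bleeding on one monotherapy, say, or aspirin against clopidogrel on NACE) from being reported as superiority, even if the primary test failed. The error rate behind such a statement would be several times the stated 5%.

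**Working it through.** **The plan's own figure first.** Inputs from SAP 5: 47% against 30%, ratio 2:1, 90% power, two-sided 0.05. The pooled-variance formula gives 127 controls and 381 in total; the arcsine formula gives exactly 384. With 256 against 128, power is 90.3%. Loss of 20%: 384/0.8 = 480. The primary design reproduces with one test at 0.05.

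**Counting the secondary tests.** SAP 9.3 has 5 binary + 1 ordinal + 4 time-to-event = 10 secondaries. Items 1 and 3 end before randomisation, which leaves 8 that include post-randomisation time. With five comparisons each, that is 8 × 5 = 40 tests and 40 × 0.05 = 2 expected false positives if nothing differs.

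**Why the formula 1 − 0.95^k is not enough.** The five comparisons of one endpoint overlap. Independence would give 1 − 0.95^5 = 22.6% per endpoint; simulation gives about 12.8%. For 40 tests, independence would give 87%, which overstates.

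**Simulation.** Three equal arms, no effect, 100,000 replicates, normal approximation. For arm values A (DAPT), B and C:

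- pooled: z = (A − (B + C)/2)/√1.5
- pairwise: z = (difference)/√2
- each z is compared with 1.96
- three-group: sum of squared deviations from the mean, against the 95% point of chi-square with 2 df

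Endpoints share an equal correlation rho. The documents give no value, so 0 to 0.8 is an assumption.

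| Set | Tests | rho 0 | rho 0.5 | rho 0.8 |
|---|---|---|---|---|
| Four time-to-event, pooled only | 4 | 18.4% | 15.4% | 11.4% |
| Four time-to-event, all five comparisons | 20 | 42.1% | 35.5% | 26.8% |
| Eight secondaries, pooled only | 8 | 33.4% | 24.7% | 15.6% |
| Eight secondaries, all five comparisons | 40 | 66.3% | 52.3% | 35.1% |

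Check: 1 − 0.95^4 = 18.5% and 1 − 0.95^8 = 33.7%, close to the pooled-only values at rho 0.

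**Overlapping, rare endpoints.** A second simulation had 160 per arm, haemorrhage nested in all bleeding, TLF within NACE, and stent thrombosis within TLF. All outcomes were treated as binary. Rates were assumed: haemorrhage 0.3-2% per half-year, other bleeding 3-10%, TLF 1-4%, lesions 35-60%, symptoms 30-40%. It gave 27-30% for the eight pooled tests and 50-59% for all 40.

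**Interactions.** SAP 9.6 lists nine subgroup factors. One splits prior gastrointestinal bleeding at 24 months, and exclusion 7 empties its recent level. Eight remain: 1 − 0.95^8 = 34% on the primary endpoint alone, if the factors are independent.

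**Not counted.** Per-protocol repeats; MACCE (SAP 9.4); and the extra time windows in SAP 4.2, because SAP 9.3 and the table listings analyse the affected endpoints over 12 months.

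**The case against.** The strongest reply is that the only stated hypothesis and main aim concern the primary endpoint. No passage says that a secondary result supports a confirmatory claim or stands if the primary fails. Unadjusted secondaries beside one controlled primary are common and usually read as supportive. This stands as far as intent goes, and it is why the primary conclusion is safe. It does not remove the written superiority test, nor explain why the exploratory label stops at 9.2.

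A second reply is that the Cox sentence names the primary endpoint, so the superiority test may not apply to the secondaries. On that reading the paragraph would add a second full-alpha test of the primary beside the logistic test in 9.2. On the other reading it governs the four secondaries listed beneath it. Either way the sentence needs correcting.

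Two stronger readings are tempting, and the documents do not support them:

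- A reader might infer that SAP 9.3 sets superiority tests for the whole secondary family. It does not. The word is confined to 9.3.2; section 9.3.1 plans odds ratios from logistic models with intervals and p-values, and the 5% level there comes from 9.1.
- A reader might infer that a chance significant secondary is likelier than not. That holds only for the full set of comparisons at low to moderate correlation. Pooled-only tests of the eight stay at or below about 33%, the four time-to-event endpoints reach at most 42%, and the full 40 tests fall to 41% at rho 0.7. High correlation is plausible: endpoint 5 contains 4, endpoint 9 contains 8, and endpoints 7 and 9 share BARC 2-5 bleeding.

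**Conclusion.** The point holds as a gap in error control and labelling for the secondary analyses. With no true difference, at least one nominally significant result is expected in about 11-18% of trials for the four time-to-event endpoints on the pooled contrast, 27-42% with all five comparisons, and 35-66% for the eight secondaries with all five. The figures assume no effect on any secondary, equal arms, equal correlation between 0.8 and 0, and a normal approximation; sparse endpoints such as stent thrombosis would contribute less. The documents supply neither the correlation nor secondary event rates. Even the narrowest count is more than twice 5%. The primary test, its alpha and its sample size are unaffected. The change should be made because it settles what the trial may claim.

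**What to change.** 1. In SAP 9.3 and 9.6, state that the pooled monotherapy against DAPT test of the primary endpoint is the only confirmatory test. Correct the endpoint named in the Cox sentence of 9.3.2. For secondaries, replace the superiority test with an estimate, 95% CI and nominal p-value, not adjusted for multiplicity. Label the three-group, pairwise and interaction analyses exploratory, as 9.2 already does for the primary endpoint's group comparisons.
2. If a confirmatory secondary claim is wanted, test only listed endpoints, on the pooled contrast, in fixed sequence at two-sided 0.05 after a significant primary test, stopping at the first failure. An example is endpoint 2 (lesions after randomisation), then endpoint 4 (clinically evident haemorrhage after randomisation). Endpoint 2 combines incidence and severity, so the SAP must name which one is tested.
3. Optionally, test the three pairwise comparisons of the primary endpoint at 0.05 only after a significant pooled test. With three arms, any two pairwise nulls imply that all arms are equal, so closed testing holds family-wise error at 5%. Simulated with 128 per arm and 47% in every arm, any pairwise rejection falls from 12.6% ungated to 4.4% gated.

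The cost is SAP wording, with no new patients, data or endpoints. The downside is that secondary and subgroup p-values can no longer be reported as superiority findings outside the sequence.
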